### Main analyses

Analyses for the main results will be conducted by the researchers with assistance from a statistician. Data will be inspected for normality and nonparametric statistics applied where appropriate. Percentage weight loss will be computed. Scores on cognitive measures will be transformed into z-scores. Linear mixed models will be used to compare differences between treatment groups in percentage weight loss, executive function, binge eating and to examine whether change in executive function predicted changes in weight and binge eating.

### Secondary analyses

To examine the baseline and prospective relationships between biological data and cognition/weight, linear or logistic regression analyses will be performed whilst controlling for potential confounders. The Bonferroni correction or FDR (False Discovery Rate) method will be used for multiple comparisons and post-hoc testing will be performed where appropriate. Secondary analyses for the other secondary measures will use either linear mixed models or repeated measure analysis of variance (ANOVA). We will report the main analyses in a separate publication to secondary analyses.

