**Methods/design:**

One hundred and seventy-six obese participants will be randomly assigned to one of two groups: (1) behavioural weight loss alone (BWL) group = 8 sessions of individual BWL sessions plus 12 group BWL sessions or (2) Cognitive Remediation Therapy for Obesity (CRT-O) plus BWL group (CRT-O + BWL) = 8 sessions of individual CRT-O plus 12 group BWL sessions. The study is double blind – participants will only be told that two weight-loss treatments are being compared and research assistants conducting outcome assessments will not know participants’ group allocation. Blood tests will be conducted to measure inflammatory markers. Measurement points will be at baseline, post treatment and 1-year follow-up. The primary outcomes will be differences between treatment groups in percentage weight loss, executive function, binge eating and an examination of whether changes in executive function predict changes in weight and binge eating. Secondary outcome measures will examine changes on inflammation, quality of life, and grazing behaviour and whether these predict changes in executive function and weight.

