*Trail Making Test* (TMT) [29]: this will be used to assess psychomotor speed, visual integration, cognitive flexibility and inhibitory control. This test measures the subject’s ability to connect written numbers in an ascending order (Trail A), and, afterwards, to connect numbers and letters, alternating numbers in ascending order and letters in alphabetical order (Trail B), for example, 1-A-2-B. The score is the response time taken to complete the respective trails [28]
*Behaviour Rating Inventory of Executive Function* (BRIEF-A): participants will complete the BRIEF-A Self-report Form. This instrument is a 75-item standardised measure that records views of an adult’s executive functions or self-regulation in a person’s everyday environment. It has been shown to be a reliable and valid measure of executive functioning in individuals across a broad age range [30]
*Memory: Wechsler Memory Scale* (WMS), *Logical Memory Subtest*: the Logical Memory Test is the most widely used measure of memory [31], and it targets auditory-linguistic memory. The task demands verbal recall of spoken story passages
*Language: Boston Naming Test* (BNT): the BNT is a 60-item confrontation naming test which is considered to be a reliable measure of word retrieval performance [32]
*Nutrition*: a comprehensive assessment, using a 1-week food diary, will be conducted by a dietitian and will be analysed using FoodWorks software. The Foodworks Professional package includes food composition tables and contains nutrient values for more than 4200 foods, beverages and supplements. FoodWorks is suitable for dietary analysis and meal planning
*Inflammatory markers*: tumor necrosis factor-α (TNFα), interleukin-6 (IL-6), inflammasome-activated IL-1β and C-reactive protein will be measured
*Clinical assessment*: a brief clinical assessment will verify comorbidities such as an eating disorder, depression or anxiety. The participant will also be asked questions related to their previous weight-loss attempts and beliefs about weight loss. The following measures will also be completed:

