#### Power calculations

We calculated the sample size with a method that takes into account the intracluster correlation coefficient (*r* = .02) for comparison between groups using a two-tailed linear mixed model, predicting a small effect size (Cohen’s *d* of 0.2) on weight loss and using a power of 80%, and determined that a sample size of 70 individuals per group is needed. Assuming an attrition rate of 25% per group, a sample of 88 per group is necessary, totalling 176 participants.

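### The secondary analyses allow Bonferroni or FDR without saying which applies; where family-wise control is meant, Holm should replace plain Bonferroni

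*Protocol article*

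**What the plan says.** The section Secondary analyses plans linear or logistic regressions for the "baseline and prospective relationships between biological data and cognition/weight", adjusted for confounders. It then states: "The Bonferroni correction or FDR (False Discovery Rate) method will be used for multiple comparisons". It does not say which method goes with which tests, how the choice is made or what FDR level applies. The section Main analyses does not settle it.

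The number of tests is not given. The section Assessment lists four markers ("tumor necrosis factor-α (TNFα), interleukin-6 (IL-6), inflammasome-activated IL-1β and C-reactive protein will be measured"), three dependent measures from the card-sorting test, two Trail Making times and the BRIEF-A, besides memory and language tests. The section Power calculations describes a "two-tailed linear mixed model" but gives no significance level.

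**The concern.** The two named methods offer different guarantees. After Bonferroni, a reader may take it that the chance of even one false positive in the family is at most 5%. After an FDR procedure at 5%, the reader may take it only that false positives make up at most 5% of the declared findings on average. A plan that joins the two with an *or* is satisfied by either, so the text does not tell the reader which guarantee a reported association will carry. The per-test thresholds also diverge as more hypotheses are rejected, so the list of declared associations can differ on the same data.

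Separately, one of the two options is inefficient. Holm's step-down procedure controls the same family-wise error rate as Bonferroni, needs no further assumptions and rejects everything that Bonferroni rejects. Where family-wise control is wanted, plain Bonferroni has no advantage in error control. At stake is some power, and clarity of interpretation, in the analyses linking inflammation to cognition and weight.

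**Working it through.** The plan states no multiplicity figure, so there is none to reproduce. The check compares the permitted rules, and Holm, under stated assumptions.

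**Inputs from the document.** Four markers; six executive-function scores (3 card-sorting, 2 Trail Making, 1 BRIEF-A); weight; 176 participants; 25% attrition, so 176 × 0.75 = 132 completers.

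**Assumptions.** Two-sided level 0.05. Number of tests m from 4 (four markers, one outcome) to 28 (4 markers × 7 outcomes). True correlation 0.25, and correlation 0.3 between test statistics. None of these is in the document.

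**Step 1: thresholds.** For the i-th smallest p-value:
- Bonferroni: 0.05/m for every i
- Holm: 0.05/(m − i + 1), stopping at the first failure
- Benjamini-Hochberg (BH): i × 0.05/m

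Bonferroni gives 0.05/4 = 0.0125, 0.05/8 = 0.00625, 0.05/16 = 0.0031 and 0.05/28 = 0.0018. At i = 1 all three thresholds equal 0.05/m. BH then rises to 0.05 at i = m, so it exceeds Bonferroni by a factor of i, from 1 up to m. Holm's threshold is never below Bonferroni's.

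**Step 2: power for one correlation under Bonferroni.** Power ≈ Φ(atanh(0.25) × √(n − 3) − z), where z is the two-sided critical value at 0.05/m. For n = 132, atanh(0.25) × √129 = 2.90.
- m = 4: Φ(2.90 − 2.50) = 0.66
- m = 8: 0.57
- m = 16: 0.48
- m = 28: Φ(2.90 − 3.12) = 0.41

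Baseline associations could use up to 176 participants. Power is then 0.81 for m = 4 and 0.59 for m = 28.

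**Step 3: mean number of rejections** (simulation, n = 132, r = 0.25, correlation 0.3 between tests).

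| True effects / tests | Bonferroni | Holm | BH | Runs where BH declares more than Bonferroni |
|---|---|---|---|---|
| 4 / 4 | 2.6 | 3.0 | 3.2 | 42% |
| 4 / 8 | 2.3 | 2.4 | 2.9 | 44% |
| 8 / 16 | 3.9 | 4.1 | 5.7 | 80% |
| 14 / 28 | 5.8 | 6.2 | 9.9 | 93% |

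The Holm gain is 3.0 − 2.6 = 0.4 and 6.2 − 5.8 = 0.4 in the first and last rows. With a single true effect it is negligible: 0.69 to 0.70 for m = 4, and 0.461 to 0.463 for m = 28. BH then declares more than Bonferroni in only about 3% of runs. Holm never rejected fewer than Bonferroni.

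**Step 4: what the rules trade.** In a separate simulation (independent tests, half of the effects true, each with 80% power at an unadjusted 0.05), Bonferroni / Holm / BH gave:
- chance of at least one false positive: 0.025 / 0.036 / 0.093 for m = 8, and 0.024 / 0.032 / 0.150 for m = 16
- average power per true effect: 0.527 / 0.560 / 0.675 for m = 8, and 0.438 / 0.467 / 0.665 for m = 16

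BH gains about 15 points (0.675 − 0.527) and 23 points (0.665 − 0.438) over Bonferroni, and pays with a higher family-wise error. Holm gains about 3 points (0.560 − 0.527 and 0.467 − 0.438) and keeps the family-wise error below 0.05.

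**The case against.** The strongest reply concerns scope. This is a journal article; which correction applies to which secondary family, and at what level, is ordinarily settled in the statistical analysis plan, which is not shown. The article commits to correcting for multiplicity, both methods are legitimate, and nothing it says is false. This largely stands: the absence of a list of tests is not a fault here, and FDR against family-wise control is a trade-off on which the sponsor may decide either way. Bonferroni is conservative rather than wrong, and Holm's gain is often small.

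A reader might also infer more than the text supports:
- *That the rule will be picked once the p-values are known.* No section says when the choice is made; all that can be said is that this article does not make it.
- *That one rule would typically yield no association and the other several.* Bonferroni found nothing while BH found something in only about 0.3% to 1.5% of simulated runs, because the smallest p-value faces the same threshold under both.
- *That Bonferroni makes the inflammation hypothesis nearly untestable.* Power for one correlation of 0.25 is 41% to 66% with 132 participants and 59% to 81% with 176. Bonferroni found at least one association in 94% (4 of 4 true) and 96% (14 of 28 true) of runs.

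What survives is narrower: the text names two non-equivalent rules without a criterion, and one of them has a uniformly better substitute at the same error rate.

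**Conclusion.** The point holds as a minor one. The rule as written lets the number of declared associations depend on an unstated choice: BH declared more than Bonferroni in 42% to 93% of runs with half or all of the effects true, but in about 3% with one true effect. Replacing Bonferroni with Holm is an improvement at the same family-wise guarantee, worth from almost nothing with one true effect to about 0.4 detections with 4 of 4 or 14 of 28 true.

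These sizes rest on the assumed correlation of 0.25, 132 completers, correlation 0.3 between tests and a family of 4 to 28 tests. That Holm is never worse than Bonferroni rests on none of them. Only secondary analyses are affected, and the primary treatment comparison does not change.

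**What to change.** In Secondary analyses, replace Bonferroni with Holm wherever family-wise control is intended. For the analyses of markers against cognition and weight, name one rule before results are seen: Holm, or Benjamini-Hochberg at a stated level with its findings reported as exploratory. If an analysis plan already makes this choice, a reference to it is enough.

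The cost is a change of wording, since all three procedures use the same p-values. Holm in place of Bonferroni carries no statistical penalty. Choosing Benjamini-Hochberg means accepting a weaker error guarantee in return for more detections, which is why its findings should be labelled exploratory.

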## Discussion

If CRT-O (plus BWL) is successful at assisting people to lose weight and to maintain the weight loss it would allow for the development of an intervention that could significantly improve treatment outcomes. Given the poor long-term outcomes for previously investigated treatments (excepting bariatric surgery reserved for the most severe cases) and the increasing public health burden of obesity, novel and integrative treatment approaches are urgently needed.

Our RCT is designed to compare two groups, a CRT-O (plus BWL) group to a BWL alone group. We will investigate whether CRT-O (plus BWL) is effective in improving a person’s ability to lose weight, to maintain their weight loss and to improve their executive functioning, compared to BWL alone. The strengths of our design include its large sample size, the use of validated and standardised assessments, and its double-blind study design. We will also be the first to measure inflammatory markers to discern whether there is an association between inflammation, weight and executive function in obese individuals.

### Trial status

Trial has started recruiting participants in September 2016.

## Abbreviations

BED: Binge-eating disorder
BMI: Body Mass Index
BNT: Boston Naming Test
Brief-A: Behaviour Rating Inventory of Executive Function
BWL: Behavioural weight-loss intervention
CRT: Cognitive Remediation Therapy
CRT-AN: Cognitive Remediation Therapy for Anorexia Nervosa
CRT-O: Cognitive Remediation Therapy for Obesity
DASS: Depression, Anxiety, Stress Scale
EDE-Q: Eating Disorder Examination Questionnaire
GCS: Group Climate Scale
GQ: Grazing Questionnaire
SF-12: Short Form-12 Health Status Questionnaire
TMT: Trail Making Test
WAI: Work Alliance Inventory
WCST: Wisconsin Card Sorting Test
WMS: Wechsler Memory Scale
